##### Data collection and management

Baseline data, underlying diseases, comorbidities, and the Acute Physiology and Chronic Health Evaluation II score on day 1 will be collected. Daily vital signs, Sequential Organ Failure Assessment score, and mechanical ventilation parameters will be monitored. Blood gas results will be collected before treatment, during the first 7 days, and at discharge. For patients receiving invasive mechanical ventilation at enrolment or on day 7, lower respiratory tract aspirates (endotracheal aspirates, ETAs) will be collected *via* the endotracheal tube using aseptic techniques. For patients who have been extubated by day 7 and can expectorate effectively, spontaneously expectorated deep sputum specimens will be collected. Blood samples collected on days 1 and 7 will be used to measure citrullinated histone H3 by enzyme-linked immunosorbent assay and cell-free DNA concentration.

Primary and secondary outcomes will be evaluated by independent assessors blinded to treatment allocation using standardized case report forms. To ensure data security, all source data will be anonymized using unique study IDs and stored on a password-protected server. Missing data will be minimized through standardized follow-up procedures. The amount, timing, and reasons for missing data will be summarized by randomized group.

##### Safety monitoring

During inhaled NO administration, NO2 will be continuously monitored and maintained below 3 ppm. MetHb levels will be measured 15 min after the initiation of each inhaled NO treatment session and at the end of each session. Renal function will be assessed daily using blood testing. An independent Data and Safety Monitoring Board (DSMB), comprising two external clinicians and one biostatistician, will review safety data every 6 months. No formal interim analysis of efficacy or futility and no sample-size re-estimation are planned. Serious adverse events will be reported within 24 h. The final database will be locked upon completion of the 30-day follow-up and resolution of all queries. Participant recruitment and study-gas treatment will be temporarily suspended, and an ad hoc safety review by the Data and Safety Monitoring Board (DSMB) will be initiated, if any of the following occurs:Any unexpected death assessed as at least possibly related to study-gas treatment.Two or more unexpected serious adverse events assessed as at least possibly related to study-gas treatment.In the NO group, permanent discontinuation of study-gas treatment due to methemoglobin (MetHb) ≥7% or persistent inhaled NO_2_ concentrations >3 ppm in ≥10% of participants.A clinically important and unexpected imbalance between groups in the incidence of serious adverse events, severe hypoxemia, or hemodynamic instability.A major breach of blinding, major protocol deviation, or data-integrity issue that may jeopardize participant safety or seriously compromise trial validity.

##### Statistical analysis

Statistical analyses will be performed using R in RStudio. Changes in CPIS, 28-day ventilator-free days, vasopressor-free days, antibiotic-free days, ICU-free days, hospital-free days, CPIS and SOFA scores, PaO_2_/FiO_2_ ratios, and serum creatinine levels will be assessed for normality. Normally distributed continuous data will be expressed as mean ± SD and compared between groups using the independent-samples t test. Non-normally distributed continuous data will be expressed as median and interquartile range, M (Q1, Q3), and compared using the Wilcoxon rank-sum test. In-hospital mortality, ICU mortality, 28-day mortality, the incidences of MetHb levels ≥5%, ≥7%, and ≥10%, inhaled NO_2_ concentrations ≥3 ppm, airway hyperreactivity events, and AKI stages 1, 2, and 3 during hospitalization will be expressed as *n* (%) and compared between groups using the chi-square test or Fisher’s exact test, as appropriate. A P value less than 0.05 will be considered statistically significant.

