#### Randomization and blinding

Participants will be randomly assigned in a 1:1 ratio to the high-dose inhaled NO group or the control group using a computer-generated simple randomization sequence. Allocation concealment will be maintained by an independent unblinded research staff member who is not involved in participant screening, clinical care, outcome assessment, data collection, or statistical analysis and who will retain the randomization codes.

Both groups will use identical NO delivery devices, respiratory circuit connections, treatment frequencies, and treatment durations. In the high-dose inhaled NO group, the device will operate in its standard mode to deliver the protocol-specified NO concentration. In the control group, the device will operate in a sham NO research mode. This mode will maintain the same user interface, operating procedures, and display of study-related parameters as in the intervention group, but will deliver gas containing no NO (NO concentration, 0 ppm).

For each treatment session, the independent unblinded research staff member will perform device connection, mode selection, parameter setting, and operational verification. This staff member will not participate in clinical care, outcome assessment, data collection, or statistical analysis and will not disclose device mode or treatment allocation to other study personnel or the clinical team. Participants, treating physicians, bedside clinical staff, outcome assessors, data collectors, and statisticians will remain blinded to treatment allocation.

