#### Sample size

As no previous studies have reported the effect of high-dose inhaled NO on CPIS outcomes in patients with severe pneumonia caused by MDR bacteria, the sample size was estimated using preliminary retrospective data from our center. These data included four patients who received high-dose inhaled NO and 11 patients who received standard treatment. The between-group difference in CPIS was 3 points, with a standard deviation of 4 points. Assuming a two-sided α of 0.05 and a β of 0.20 (80% power), at least 28 participants per group are required, for a total of 56 participants. Allowing a 10% dropout rate, the target sample size is 64 participants with confirmed MDR bacterial infection (32 per group). Assuming that 65% of patients with suspected MDR infection will have confirmed MDR bacterial infection, approximately 98 patients with suspected MDR infection will need to be enrolled.

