#### Outcomes

##### Primary outcome

The primary outcome is the change in CPIS from baseline to day 7.

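### The primary comparison of change in CPIS has no baseline covariate, and a normality check on the trial data chooses the test, so precision may be lost and the effect measure is not fixed in advance

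*Protocol article*

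**What the plan says.** The Primary outcome section states: "The primary outcome is the change in CPIS from baseline to day 7". Under Statistical analysis, change in CPIS is one of a list of continuous variables that "will be assessed for normality". Variables judged normal are summarised as mean ± SD and "compared between groups using the independent-samples t test". Those judged non-normal are summarised as median and quartiles and "compared using the Wilcoxon rank-sum test". The section names no covariate and does not say how normality is judged.

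The Subgroup and sensitivity analyses section adds three subgroup factors and a per-protocol analysis, but no baseline-adjusted analysis. Allocation is made "using a computer-generated simple randomization sequence". Table 1 schedules CPIS on days 1, 3 and 7. The Sample size section rests on a difference in means: "The between-group difference in CPIS was 3 points, with a standard deviation of 4 points".

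**The concern.** There are two separate weaknesses.

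**Efficiency.** A change score fixes the slope of day-7 CPIS on baseline CPIS at 1. If the true slope differs from 1, as regression to the mean often makes it, the change stays correlated with baseline, and a model that estimates the slope is more precise. The trial has to record baseline CPIS anyway to form the change. Power is set at 80%, and the assumed difference and SD come from only 4 treated and 11 untreated retrospective patients, so spare precision would be useful.

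**Effect measure.** A t test estimates a mean difference, while a rank-sum test compares distributions by rank and would be reported here with medians. Which of them becomes the primary result is settled only after the outcome data are examined. The sample size supports the mean difference only.

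**Working it through.** **Inputs from the article:** difference 3, SD 4, two-sided α 0.05, power 80%, 28 evaluable per group, 10% dropout, 64 confirmed MDR participants, 65% confirmation rate.

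**Inputs that are not in the article, so assumed and varied:** the baseline to day-7 correlation ρ, and k = baseline SD / day-7 SD. The article also does not say whether SD 4 belongs to the change or to the score. The main calculation takes it as the SD of the change.

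**1. The plan's own figures.** n per group = 2 × (1.96 + 0.84)² × 4² / 3² = 27.9, so 28. Then 28 / 0.9 = 31.1, so 32 per group and 64 in total, and 64 / 0.65 = 98.5, consistent with the stated figure of approximately 98. All reproduce. Power with 28 per group is 80.1% by the normal formula and 78.7% by the exact t test.

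**2. Unadjusted power at the expected evaluable number.** 64 × 0.9 = 57.6, or 28.8 per arm. The exact t test gives 79.9%.

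**3. Power with baseline as a covariate.** The variance of the treatment effect under ANCOVA, relative to the change-score comparison, is

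(1 − ρ²) / (1 + k² − 2ρk),

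which reduces to (1 + ρ)/2 when k = 1. The effective SD is 4 times the square root of this ratio. For example, k = 1 and ρ = 0.5 give a ratio of 0.75 and an SD of 3.46. Power at 28.8 per arm:

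| k | ρ = 0.3 | ρ = 0.5 | ρ = 0.7 |
|---|---|---|---|
| 0.5 | 81.5% | 79.9% | 82.7% |
| 0.6 | 83.4% | 80.4% | 80.6% |
| 0.75 | 87.1% | 82.9% | 80.1% |
| 1 | 93.4% | 89.8% | 85.8% |
| 1.25 | 97.7% | 95.9% | 94.2% |

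The gain disappears where the true slope ρ/k equals 1, as at k = 0.5 and ρ = 0.5. The only cost of adjustment there is one degree of freedom.

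**4. If SD 4 is the SD of the score.** With equal SDs at both times, the SD of the change is 4√(2(1 − ρ)) and the ANCOVA residual SD is 4√(1 − ρ²). With 28 per group (normal formula), power for change score against ANCOVA is 66% against 84% at ρ = 0.3, 80% against 90% at ρ = 0.5, and 95% against 98% at ρ = 0.7.

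**5. The test-selection rule.** This was simulated with 20,000 trials, 28 per arm, normal scores rounded to integers, ρ = 0.5, equal SDs and SD of change 4. The article names no normality test, so Shapiro–Wilk at 5% in either arm is an assumption.

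| Analysis | Type I error | Power at difference 3 |
|---|---|---|
| t test | 5.3% | 78% |
| Rank-sum | 5.1% | 76% |
| Two-stage rule | 5.5% | 78% |
| ANCOVA | 5.4% | 88% |

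The Monte Carlo standard error for type I error is about 0.15 percentage points. The check sent about 14% of trials to the rank-sum test although the underlying scores were normal. This shows that the effect measure can change under the rule. It does not show that error rates suffer.

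**The case against.** The strongest defence is that an unadjusted comparison of randomised groups is valid and covariate adjustment is a refinement. That is correct, and it rules out several stronger readings.

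- A reader might infer that the analysis ignores baseline CPIS. It does not: the change subtracts it. Only covariate adjustment is absent.
- A reader might infer that simple randomisation of a small trial biases the result through baseline imbalance. Chance imbalance is random error, already reflected in the confidence interval and P value. Adjustment would reduce that error, but there is no bias to remove.
- A reader might infer that choosing the test from the data inflates type I error. The simulation gives 5.5% against 5.3% for the plain t test, with the same power.
- A reader might take 86–93% as the power that adjustment would deliver. That range needs equal SDs at baseline and day 7. All participants enter invasively ventilated with recently diagnosed severe pneumonia, so baseline scores may well be narrower than day-7 scores, and the gain could then be close to nothing.

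A further defence is that a separate analysis plan, mentioned under Data Availability, may settle adjustment. This softens the point but does not remove it, because the article itself names the tests and the rule for choosing between them.

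**Conclusion.** The point stands as one of efficiency and an unfixed effect measure. The planned test is not invalid, and the article's sample size arithmetic is not wrong for the analysis it describes.

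The size of the efficiency loss is uncertain. Against 79.9% unadjusted, adjusted power is about 80–87% for a baseline SD of 0.5–0.75 of the day-7 SD, 86–93% for equal SDs, and more if the baseline SD is the larger, all for ρ between 0.3 and 0.7. These figures rest on SD 4 being the SD of the change and on 28.8 evaluable per arm.

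The unfixed effect measure does not depend on those assumptions: it follows from the text alone. A change is worth making because it costs nothing and, apart from one degree of freedom, gives up no precision at this sample size. How deaths before day 7 enter the primary outcome is a separate matter that adjustment does not settle.

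**What to change.** For the primary outcome, replace the normality-driven choice with a single prespecified model: ANCOVA of day-7 CPIS (or, equivalently for the treatment effect, of the change) on arm and baseline CPIS. Report the adjusted mean difference with its 95% confidence interval.

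Name one standard-error method in advance, for example model-based, or an HC-type robust estimator with a t reference distribution. Leaving that choice open would replace one undecided element with another. At 28 per arm the detail matters: in simulation, robust errors with normal critical values gave type I error of 5.9% (HC1) to 6.5% (HC0), against 5.3% both for HC1 with a t reference and for model-based ANCOVA.

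Keep the rank-sum test as a sensitivity analysis only. Baseline adjustment can be used in the same way for day-3 CPIS and for SOFA on days 3 and 7. It does not by itself deal with the daily PaO2/FiO2 series, which consists of repeated measures.

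The cost is wording, with no extra patients or measurements. The change should be made before any unblinded outcome data are seen.

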##### Secondary outcomes

 In-hospital mortality, ICU mortality, and 28-day mortality.Ventilator-free days, vasopressor-free days, antibiotic-free days, ICU-free days, and hospital-free days through day 28.CPIS and Sequential Organ Failure Assessment (SOFA) scores on days 3 and 7.Microbiological eradication rate on day 7.Concentrations of citrullinated histone H3 and cell-free DNA.Daily ratio of arterial oxygen partial pressure to fractional inspired oxygen (PaO_2_/FiO_2_) from days 1 to 7.

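### One unadjusted P<0.05 rule covers the primary outcome and some 13 to 22 secondary comparisons, and the daily measures are given only two-sample tests

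*Protocol article*

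**What the plan says.** There is one primary outcome: "The primary outcome is the change in CPIS from baseline to day 7". The sample size is built on it alone: "Assuming a two-sided α of 0.05 and a β of 0.20 (80% power), at least 28 participants per group are required".

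The Secondary outcomes section lists three mortality measures, five kinds of free days to day 28, "CPIS and Sequential Organ Failure Assessment (SOFA) scores on days 3 and 7", microbiological eradication on day 7, two biomarkers (citrullinated histone H3 and cell-free DNA), and "Daily ratio of arterial oxygen partial pressure to fractional inspired oxygen" over days 1 to 7. Serum creatinine on days 1 to 7 is a safety outcome. Table 1 schedules both PaO2/FiO2 and creatinine on each of the seven days.

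The Statistical analysis section names change in CPIS in the same sentence as the free days, the CPIS and SOFA scores, PaO2/FiO2 and creatinine. All of these go to an independent-samples t test or a Wilcoxon rank-sum test, depending on normality. Mortality and the binary safety outcomes go to a chi-square or Fisher test. The section names no test for eradication or the biomarkers. It ends with one rule for everything: "A P value less than 0.05 will be considered statistically significant". In the Discussion, only the mechanistic assessments are called exploratory.

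**The concern.** The article does not merely stay silent on multiplicity. It states a decision rule, and that rule gives a secondary or safety comparison the same standing as the primary outcome. The Discussion says the trial will judge whether treatment improves bacterial clearance, clinical outcomes and mortality. If change in CPIS misses, the published rule still lets any one of many other comparisons be declared significant.

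Two features add to this. Day-7 CPIS is tested beside change in CPIS to day 7; under randomization both estimate the same treatment effect, so the same question gets two tests. And the only methods offered for PaO2/FiO2 and creatinine are tests that take one independent value per patient. Applied to seven daily values, they must either be repeated day by day, among whoever is still alive and sampled, or be run on pooled patient-days that are not independent.

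**Working it through.** **The plan's own figure.** Inputs from the Sample size section: difference 3, SD 4, two-sided α 0.05, power 80%; 1:1 allocation from the Randomization section.

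- n per group = 2 × (1.960 + 0.842)² × 4² / 3² = 27.9, so 28; power 80.1% by the normal approximation.
- 28 / 0.9 = 31.1, so 32 per group and 64 in total.

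The stated figures reproduce. They concern one test at 0.05. The article gives no count of comparisons and no family-wise error rate.

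**Counting the secondary comparisons.**

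| Reading | Mortality | Free days | CPIS/SOFA, days 3 and 7 | Eradication | Biomarkers | PaO2/FiO2 | Total |
|---|---|---|---|---|---|---|---|
| Only outcomes with an assigned test, PaO2/FiO2 once | 3 | 5 | 4 | – | – | 1 | 13 |
| Every listed outcome, PaO2/FiO2 once | 3 | 5 | 4 | 1 | 2 | 1 | 16 |
| Only outcomes with an assigned test, each PaO2/FiO2 day | 3 | 5 | 4 | – | – | 7 | 19 |
| Every listed outcome, each PaO2/FiO2 day | 3 | 5 | 4 | 1 | 2 | 7 | 22 |

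**Error if all nulls are true.** The expected number of false positives is k × 0.05, whatever the correlation. The chance of at least one under independence is 1 − 0.95^k.

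| k | Expected | At least one, if independent |
|---|---|---|
| 13 | 0.65 | 48.7% |
| 16 | 0.80 | 56.0% |
| 19 | 0.95 | 62.3% |
| 22 | 1.10 | 67.6% |

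**Allowing for correlation.** The article gives no correlations, so these are assumptions. Simulating 200,000 sets of 22 null normal test statistics with a common correlation gave:

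| Assumed correlation | 0.2 | 0.3 | 0.4 | 0.5 | 0.6 | 0.8 |
|---|---|---|---|---|---|---|
| At least one | 62% | 57% | 51% | 44% | 37% | 23% |

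Block structures, with stronger correlation within mortality, free days, scores and PaO2/FiO2 than between them, gave 41% to 57% for 22 tests. One such structure gave 47.5% for 19 tests.

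**Day-7 CPIS beside the primary.** Assume equal variances at baseline and day 7, with correlation ρ between them. The change and the day-7 score then correlate at √((1 − ρ)/2), which is 0.59 for ρ = 0.3 and 0.39 for ρ = 0.7. The chance that at least one of the two tests is falsely significant is 8.8% and 9.4% respectively, against 5% for the primary alone.

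**Daily measures.** Seven values per patient are scheduled (Table 1); the method is a two-sample t or Wilcoxon test (Statistical analysis). The article does not say how the days are combined.

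**The case against.** A reader might infer that a false-positive secondary result is more likely than not. The documents do not support that. The 68% needs 22 independent tests, yet the outcomes plainly overlap: three mortality measures, five free-day measures, two scores at two times, one ratio on consecutive days. Under assumed correlations the figure falls on either side of 50%, and on the narrowest count it is 48.7% even with independence. Nor is the count of 22 fixed by the text. Three listed outcomes have no assigned test, the two biomarkers are called exploratory in the Discussion, and seven separate PaO2/FiO2 tests are a natural inference, not a stated plan.

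Other parts of the defence also stand. The primary outcome is single and fixed, so listing day-7 CPIS again does not alter the primary test's error rate. A two-sample test on one day uses one value per patient and is valid in itself. A mixed model does not cure truncation by death. The safety tests do not belong in the tally: with a sham of 0 ppm, a true null for methemoglobin or NO2 thresholds is implausible. The Discussion also admits possible low power for secondary outcomes.

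It can further be said that a hierarchy or a longitudinal model may sit in the unseen statistical analysis plan, and its absence from the article is no fault. That does not remove the point, because the article states a significance rule without distinction and names the tests. A later plan that restricted significance claims would have to override that published sentence.

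**Conclusion.** The point holds in a moderate form. One unadjusted threshold governs the primary outcome and 13 to 22 secondary comparisons. With all nulls true, the chance of at least one false-positive secondary result is about 49% to 68% under independence and lower with correlation: about 23% to 62% for 22 tests at assumed common correlations of 0.8 to 0.2. The primary conclusion is not at risk. What is at risk is the standing of secondary results, above all if the primary misses. The duplicate day-7 CPIS test and the two-sample tests for daily measures are separate, smaller defects in the same section. The ranges rest on assumed correlations and on how the outcome list is read, so no single probability should be quoted as the trial's error rate.

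**What to change.** In the Statistical analysis section:

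1. Reserve the term statistically significant for the primary outcome. Report secondary outcomes as estimates with 95% confidence intervals, labelled exploratory. A prespecified hierarchy or adjustment is an alternative if some secondary claims are wanted; Bonferroni over 22 tests would mean 0.05/22 = 0.0023 each.
2. Analyse PaO2/FiO2 and creatinine each with one baseline-adjusted repeated-measures model and one prespecified treatment contrast. State that values after death are not measured and how this limits interpretation.
3. Report day-7 CPIS descriptively, not as a separate test.

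The cost is a change of wording and standard model code, with no new data. The downsides are that secondary outcomes support no significance claims and that the models rely on a missing-at-random assumption.

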##### Subgroup and sensitivity analyses

Prespecified subgroup analyses of the primary outcome will be conducted according to the presence or absence of septic shock, pneumonia type (community-acquired pneumonia [CAP] versus hospital-acquired pneumonia [HAP]), and concomitant use of inhaled antibiotics.

A sensitivity analysis of the primary outcome will be performed in the PP-MDR.

## Discussion

High-dose NO has anti-infective and oxygenation-improving effects. Several studies have suggested that inhaled NO can reduce viral load in patients with coronavirus disease 2019 and prevent postoperative pulmonary bacterial infection [3,8,10,11]. However, the effect of high-dose NO in Severe pneumonia infection has rarely been reported. This study focuses specifically on patients with severe pneumonia associated with MDR bacteria and will evaluate whether high-dose inhaled NO improves bacterial clearance, clinical outcomes, and mortality without increasing adverse reactions.

Mechanistically, high-dose NO may exert antibacterial activity by damaging bacterial DNA, proteins, and lipid structures [3], inhibiting biofilm formation by Pseudomonas aeruginosa and Klebsiella pneumoniae [16], and enhancing immune-cell phagocytosis of resistant bacteria [25]. A pathway involving neutrophil chemotaxis, activation, neutrophil extracellular trap release, and bacterial killing has also been proposed as a potential mechanism through which high-dose NO improves outcomes in severe pneumonia [16].

High-dose inhaled NO has been recommended for severe pneumonia in a Chinese expert consensus, primarily based on evidence from severe viral pneumonia [26]. Evidence for severe bacterial pneumonia remains limited. This study selects patients with MDR infection because these patients lack safe and effective treatment options, and conventional antibiotic therapy is often less effective or requires costly advanced antibiotics. If high-dose inhaled NO improves outcomes in patients with severe pneumonia associated with MDR bacteria, it may have important implications for antimicrobial resistance and patient prognosis.

This study also includes exploratory mechanistic assessments. Neutrophil number and percentage, citrullinated histone H3, and cell-free DNA concentration in plasma can reflect neutrophil extracellular trap activity and may provide preliminary clinical evidence for the proposed mechanism of action [27,28].

This study has several limitations. First, it is single-blind rather than double-blind. Because safety monitoring and clinical implementation make staff blinding difficult, medical staff will not be blinded, which may introduce bias. Second, this is a single-center study with a relatively small sample size, which may lead to selection bias and limit generalizability. Although the sample size calculation is based on the primary outcome, the study may be underpowered for mortality and other secondary outcomes.

In summary, this protocol provides a rigorous framework for evaluating high-dose inhaled NO in patients with severe pneumonia associated with MDR bacteria. By following protocol reporting standards, the study is expected to provide operational evidence to guide the optimization of treatment practice for patients with severe pneumonia associated with MDR bacteria.

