**Patients and methods:**

This prospective, single-center, double-blind randomized controlled trial will be conducted at Jiangdu People’s Hospital Affiliated with Yangzhou University from January 2026 to June 2027. Patients with suspected or confirmed severe pneumonia caused by MDR bacteria will be randomized 1:1 to standard treatment plus inhaled NO (200 ppm, twice daily for 30 min/session for 5 days) or standard treatment plus sham inhalation (0 ppm NO). The primary outcome is the change in Clinical Pulmonary Infection Score (CPIS) from baseline to day 7. Secondary outcomes include mortality, 28-day ventilator-free days, vasopressor-free days, antibiotic-free days, ICU-free days, and hospital-free days, CPIS and Sequential Organ Failure Assessment scores, microbiological eradication, citrullinated histone H3 and cell-free DNA concentrations, and ratio of arterial partial pressure of oxygen to fraction of inspired oxygen (PaO_2_/FiO_2_) ratios. Safety outcomes include methemoglobin and NO_2_ thresholds, serum creatinine, airway hyperreactivity, and acute kidney injury. Primary and secondary outcomes will be analyzed in confirmed MDR participants; safety will be assessed in participants receiving at least one study-gas administration.

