## Patients and methods

### Study design

This prospective, single-center, double-blind, randomized controlled trial will enroll consecutive eligible patients admitted to Jiangdu People’s Hospital Affiliated with Yangzhou University between January 2026 and June 2027 with suspected or confirmed severe pneumonia caused by MDR bacteria. The study flow is shown in Figure 1. The protocol follows the SPIRIT statement (Table 1; Table S1) [17].

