#### Interventions

Participants in the intervention group will receive iNO at 200 ppm two times daily, with each session lasting 30 min, for 5 days, beginning within 24 h of enrollment [8]. Both the intervention and control groups will receive standard treatment according to relevant guidelines for severe pneumonia. Standard treatment may include empirical and targeted anti-infective therapy, fluid resuscitation, vasoactive drugs, lung-protective ventilation, organ support, nutritional support, and immunomodulatory therapy as clinically indicated. Once antimicrobial susceptibility results are available, participants in both groups with confirmed MDR bacterial infection will continue the protocol-directed study intervention. For participants in whom MDR bacterial infection is not confirmed, the study intervention administered solely for research purposes will be discontinued in both groups.

Inhaled NO will be administered using the NOwill N300 Nitric Oxide Generation and Delivery System (Noling Biotechnology Co., Ltd., Nanjing, China). All device installation, mode selection, circuit connection, pre-treatment safety checks, and monitoring during treatment will be performed exclusively by designated independent research personnel who have completed manufacturer training and are qualified to operate the system. These personnel will not participate in participant screening, routine clinical care, outcome assessment, data collection, or statistical analysis.

At enrolment, inhaled NO will be delivered through the mechanical ventilator circuit. If a participant is extubated during the treatment period, inhaled NO will be administered through an interface compatible with the selected sequential oxygen therapy modality.

The NOwill N300 system may be connected to invasive ventilators, noninvasive ventilators, high-flow oxygen therapy systems, nasal cannulae, or face masks. For participants receiving invasive mechanical ventilation, the NO delivery device will be integrated into the ventilator circuit at the gas outlet, with a flow sensor and NO injection port installed. The NO injection port will be positioned upstream of the humidification chamber to enable NO delivery during the inspiratory phase.

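### The protocol calls the trial double-blind with clinicians blinded, but its limitations paragraph calls it single-blind with medical staff unblinded

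*Protocol article*

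**What the plan says.** The protocol article describes blinding in several places.

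- Abstract, Patients and methods: "This prospective, single-center, double-blind randomized controlled trial will be conducted".
- Study design: "This prospective, single-center, double-blind, randomized controlled trial will enroll consecutive eligible patients".
- Randomization and blinding: "Participants, treating physicians, bedside clinical staff, outcome assessors, data collectors, and statisticians will remain blinded to treatment allocation". The same section describes a sham mode whose interface and display match the active mode, and names an independent staff member as the only unblinded person.
- Emergency unblinding criteria: individual unblinding is allowed only in emergencies where knowing the gas received is needed for immediate care.
- Interventions: monitoring during sessions is reserved for independent trained personnel, of whom the section says "These personnel will not participate in participant screening, routine clinical care, outcome assessment, data collection, or statistical analysis".
- Safety monitoring: "MetHb levels will be measured 15 min after the initiation of each inhaled NO treatment session and at the end of each session". NO2 is monitored continuously.
- Discussion, limitations: "First, it is single-blind rather than double-blind", with the reason "Because safety monitoring and clinical implementation make staff blinding difficult, medical staff will not be blinded, which may introduce bias".

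**The concern.** A reader cannot tell from the article whether the clinicians caring for these patients will know the allocation. The limitation is not a general caution about imperfect masking. It states that medical staff are unblinded and gives safety monitoring and clinical implementation as the reasons, which amounts to saying that the blinding procedure in the methods is not workable for clinical staff.

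The answer affects specific parts of the trial. Ventilator-, vasopressor-, antibiotic- and ICU-free days depend on when clinicians wean, stop a drug or discharge. Under Temporary suspension of a treatment session, the treating physician judges whether a clinical deterioration may be related to study gas. Under Permanent discontinuation, the treating physician or principal investigator may end treatment on grounds of risk. If these people know the arm, their decisions are open to expectation bias; if they do not, the sham design protects them. The published trial also has to report its blinding, and the protocol now supports two incompatible descriptions.

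A smaller question concerns the flow of safety readings. MetHb and NO2 are both monitored during sessions and compared between groups as safety outcomes. The personnel who do the monitoring are barred from data collection, while data collectors are to stay blinded. The article does not say who sees or records these values.

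**Working it through.** No figure in the article rests on blinding, and the sample-size calculation does not use it. The check is therefore a comparison of statements.

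**Step 1: the design label.** The abstract and Study design say double-blind. The Discussion denies that label in terms. All three are current text.

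**Step 2: who is blinded, group by group.**

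| Group | Methods sections | Discussion, limitations | Conflict |
|---|---|---|---|
| Treating physicians | Blinded | Medical staff unblinded | Yes |
| Bedside clinical staff | Blinded | Medical staff unblinded | Yes |
| Participants | Blinded | Not mentioned | No |
| Outcome assessors | Blinded (also in Data collection and management, for primary and secondary outcomes) | Not mentioned | No |
| Data collectors, statisticians | Blinded | Not mentioned | No |
| Independent device personnel | Unblinded, no care role | Not mentioned | No |

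The conflict covers the first two rows and the design label, and nothing else.

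**Step 3: which account the rest of the article fits.** The sham mode, the emergency unblinding criteria and the trigger for an ad hoc safety review after a major breach of blinding all fit a double-blind trial. The limitation stands alone against them. It may be leftover text, but its specific reason prevents a reader from assuming so.

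**Step 4: the safety readings.**

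- Number of MetHb readings in a full course: 5 days × 2 sessions per day × 2 readings per session = 20 per participant. This counts readings; it does not show that any of them identifies the arm.
- Sampling in both arms: Safety monitoring ties the measurement to inhaled NO sessions. However, Table 1 schedules MetHb and NO2 without splitting by arm, Analysis of populations defines study gas as NO or sham, and Statistical analysis compares the incidences between groups. Measurement in both arms is implied.
- NO2: the matched display and the restriction of monitoring to independent personnel are real safeguards.
- MetHb: the article gives no expected value by arm and does not say who sees the result.
- Recording: those who monitor sessions may not collect data, yet the readings are outcome data. That leaves a risk that values reach people meant to be blinded.

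**The case against.** The strongest defence is that the limitation is a drafting remnant. Every operational section is written for a double-blind trial, so one sentence in the Discussion should not outweigh them. That makes a wording correction the likelier repair, but it does not remove the contradiction, and the document alone cannot settle which account is true. Reading medical staff as the independent device operator does not help either: that person has no role in care, and one unblinded operator would not make the trial single-blind.

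A reader might infer three stronger things, and the article supports none of them.

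- *That scoring of the primary outcome is unblinded.* The limitation names only medical staff. Randomization and blinding keeps outcome assessors blinded, and Data collection and management promises independent blinded assessors for primary and secondary outcomes.
- *That the false-positive rate for CPIS is inflated by a calculable amount.* Any such figure needs an assumed scoring shift between arms. The article gives no basis for its size, and the scorers are not stated to be unblinded.
- *That the MetHb and NO2 data flow would itself reveal the arm, because blinded collectors must record the values.* The display is matched, monitoring is confined to independent personnel, no MetHb value by arm is given, and the article does not say who records the readings. A journal article may also leave the routing of forms to the full protocol.

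What remains of the data-flow point is a risk: the readings could suggest the arm, and the article itself cites safety monitoring as a reason why blinding staff is difficult.

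**Conclusion.** The article is wrong as written on a basic design property. The label and the status of treating physicians and bedside staff are each stated in two incompatible ways. The conflict reaches four clinician-driven secondary outcomes and the treating physician's decisions about study gas. It does not reach the blinding of outcome assessors, and no numerical bias can be attached to it from the document. The conclusion rests on one reading: that treating physicians and bedside clinical staff are medical staff in the ordinary sense.

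The handling of MetHb and NO2 values is secondary. It is a possible route to unblinding that is cheap to close, not a demonstrated leak.

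**What to change.** **Main change.** Make the abstract, Study design, Randomization and blinding, and the Discussion limitations state one design, and list which groups are blinded.

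- If bedside staff are in fact unblinded, remove the double-blind label from the abstract and Study design, and correct the list in Randomization and blinding.
- If they are blinded, delete the limitation and its stated reason.

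The cost is wording only. It should be settled early, because blinding cannot be restored after patients have been treated.

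**Secondary safeguard.** Let the independent personnel already present at each session record per-session MetHb and NO2 for both arms on a restricted form. Withhold that form from CPIS assessors and efficacy data collectors until database lock. This needs a stated exception in Randomization and blinding and in Interventions, which now bar these personnel from all data collection. The list of who is blinded should also say whether treating physicians see the values. Safety escalation and emergency unblinding stay as written. The cost is one form and a separate data stream to merge after lock.
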